### Ethical considerations

The study has been approved by NHS West of Scotland Research Ethics Committee (Reference: 12/WS/0255). Management approval for recruiting at the Western General Hospital site has been obtained from NHS Lothian. A detailed information sheet will be provided to participants with study information and contact details. Informed consent will be obtained from all patients and partners who agree to participate in the study. Additional consent will be sought from those couples and healthcare professionals who agree to take part in post-intervention acceptability/feasibility interviews. If consent is given by participants, GPs will be advised of their patient’s involvement in the trial. Couples in the trial will consent to having their baseline summary scores communicated to the practitioners delivering the intervention; the use of outcome measures is routine practice and helps practitioners tailor their approach to couples.

#### Data storage and confidentiality

Participants will be assigned a study number. All documents will be labelled with the study number alone, and data stored on computers will only use this number. All names referred to in the interviews will be changed following transcription and saved under the assigned study number. Pre-anonymised transcripts will then be deleted.

Identifiable personal data will only be retained in the following circumstances: consent forms will be stored in a locked filing cabinet; couple names/addresses will be stored in a locked filing cabinet and a password-protected computer used in disseminating outcome measures and final report/s.

#### Risks to participants

People diagnosed and treated for cancer constitute a group that can be considered vulnerable. Consequently, considerable care is required to ensure that adequate safeguards are put in place.

Men recruited to the trial will not be in the immediate aftermath of diagnosis. Recruitment to the study will only occur when the man is at least 11 weeks past surgery. Consequently, with current waiting lists, he is likely to be approached about the study four to five months after diagnosis, and will have recovered considerably from surgery. Further, only men who score ≤60 on the sexual function domain of EPIC (the clinical threshold for potency) will be invited to participate, so that the intervention is stratified to target those men most in need of additional support.

Due to the nature of the disease, and our focus on relational and psychosexual issues, it is likely that interviews touch on sensitive areas. The team has experience of conducting interviews with couples on a range of sensitive issues and is aware of the potential emotional demands on participants. Any participant who feels they are unable to continue with an interview will be reassured that it is permitted to withdraw from the research at any time.

### User involvement

The project has been designed to have user involvement throughout. A group of men affected by prostate cancer have helped design the methods and will continue to act as consultants to the project. They have helped design the intervention, train the practitioners, construct appropriate prompts for focus groups/interview schedules, and will contribute to analysis and dissemination.

## Discussion

Prostate cancer is the most common cancer in men. Surgery is a major treatment modality for localised prostate cancer. However, after surgery, men can suffer from several side-effects like erectile dysfunction, anxiety and decreased quality of life, which impact on wellbeing, intimacy and relationship quality. Men’s partners are also influenced by these side-effects and can often experience distress and reduced wellbeing. Yet previous research has revealed that couples are not generally well supported to cope with these side-effects of surgery.

With an increase in the incidence and survival of postoperative men with prostate cancer, there are significant unmet psychosexual needs for couples affected by prostate cancer. We aim to develop a family-relational-psychosexual intervention for couples and then to test the feasibility of this support in a pilot randomised control trial. We expect that sexual and relationship functioning will be increased in couples who receive the intervention, while distress will be reduced, compared to those couples who receive standard care.

At the end of this study, we will have determined whether the intervention is effective or not, and if it is acceptable to couples and healthcare professionals. An economic analysis will estimate population costs. Therefore, the study will provide evidence about the nature of a couple-based intervention, its acceptability and influence on sexual and emotional aspects of the relationship.

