### Aims

The primary aim of the study is to determine whether a family-relational-psychosexual intervention is feasible and acceptable for couples affected by prostate cancer in the context of one care-delivery setting. Subsidiary to this, the study aims to understand what processes of randomisation are plausible for a larger trial, determine a sample-size calculation for a definitive trial, and estimate the efficacy of the intervention to increase sexual and relationship functioning.

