#### Sample size calculation

The trial aims to recruit 68 men and partners at routine follow-up after surgery, with 30% over-recruitment to enable adjustment for loss to follow-up [43]. A sample size of 68 couples was calculated using G-Power [44] based on having 90% power to detect a small-to-medium effect size *f* of 0.20 on the primary outcome (using repeated measures analysis of variance (ANOVA) and testing the within-between group interaction in this two-group design with two points of measurement (end of intervention and six-month follow-up) at an alpha level of 0.05). A small-to-medium effect on sexual function was selected based on previous intervention effects seen for couple interventions in the cancer literature [45].

Assuming a baseline mean of 33 and a standard deviation of 24 on the sexual function subscale of the EPIC [46], this study will have 90% power to detect a mean difference of 9.6 units at the 0.05 level. This will allow the study to estimate the efficacy of this intervention on the mean difference in overall sexual function (as measured by EPIC) between the intervention and control groups pre- and post-test. The standardised difference observed will be used to calculate the sample size required for a definitive trial to test the efficacy of this intervention. The anticipated effect size of *f* of 0.20 on the primary outcome is a crude estimate, as it is based on a pooled estimate of a heterogeneous selection of couple interventions for several types of cancer [45].

Based on surgical data from the locale (2009 to 2011) we estimate that there will be 500 patients who will be between 12 weeks and two years from surgery during the one-year recruitment period. The estimated recruitment rate from a prior study with a similar population and intervention design was 21% [33]. As some of the patient population will be excluded from the study based on the eligibility criteria above, we anticipate contacting approximately 420 patients to recruit 88 couples (taking account of 30% over-recruitment [43] to achieve a sample size of 68 couples completing the study).

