### Phase 1: designing the intervention

The intervention will be informed by the extant literature regarding the pragmatics and focus for the couple work. It will consist of six sessions [34,35] conducted every two to three weeks [28,47] by registered practitioners at a local voluntary sector counselling organisation. The intervention will be delivered off-site in central Edinburgh, away from the pressures of a busy outpatient hospital clinic where there is usually limited time to discuss psychosexual concerns during healthcare consultations [24].

The content of the intervention will comprise assistance with emotional disclosure [33,48], psycho-education [19,29], relational and sexual needs [29-31] and dyadic adjustment and coping [49,50]. A treatment manual will be developed to guide delivery of the intervention [51]. The manual will comprise information about prostate cancer and its effects, principles of therapeutic change, guidance on using the manual and a detailed session structure plan. This manual-based family-relational-psychosexual support will be based on systemic principles [52-55] combined with techniques from sex therapy, that is, sensate focus [56]. Therefore, the manual aims to integrate components of systemic theory with elements of sex therapy to support intimacy and emotional aspects of the couple relationship.

Specialist training in delivery of the intervention will be provided to practitioners holding accredited counselling or psychotherapy qualifications. Training will include sessions led by men affected by prostate cancer and a systemic practitioner in cancer care. Fidelity to the manual will be assessed as an ongoing process, recorded by practitioner self-report using a checklist provided by the research team.

In line with routine counselling interventions, this study adopts a waiting-list control design [57]. The control group will be offered the intervention if the analysis indicates a significant benefit in quality of life for couples who receive the support.

The session structure for the intervention will cover six main topic areas as follows:

**Session 1 - Getting to know the couple: orientation and engagement.** This first session will outline the support on offer. Topics for discussion will include:

● the couple’s definition of current issues, concerns and problems

● the cancer diagnosis and treatment(s)

● the partner’s role in the context of diagnosis and treatment

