#### Data collection

As this is a feasibility study, it is not formally testing hypotheses. Nevertheless, we will examine outcome measures pre/post/follow-up (baseline, end of intervention and six-month follow-up) to evaluate the indicative effect of the intervention on both individual and couple/relational issues. Outcome measures have been selected to prevent over-burdening participants (by capping the length and number of measures used). We have generously estimated that all measures may take 30 minutes to complete, but feel that many participants will complete them in 10 minutes. Validated measures, detailed below, will be used alongside a specially designed *pro forma* for collating additional information on health-service use and demographic data.

In order to assess the feasibility and acceptability of the intervention, practitioners will complete adherence checklists, indicating for each couple which components of the intervention were covered in the therapy.

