#### Statistical analysis

Although hypothesis testing should proceed cautiously in a feasibility/acceptability study, we anticipate that couples in the intervention group will show increased scores for sexual functioning (measured using EPIC) and functional couple relationship (SCORE 15 measure), and decreased scores for anxiety and depression (HADS measure).

The study will therefore estimate the efficacy of this intervention based on the mean difference in primary (EPIC) and secondary outcome measures (SCORE 15, HADS) between the intervention and control groups pre- and post-test. Baseline demographic characteristics will be reported as mean and standard deviation for continuous data and number (percentage) for categorical data. ANOVA will be used to test the within-between group interaction in this two-group design, with two points of measurement (end of intervention and six-month follow-up). Data will be managed and analysed using SPSS version 19 (IBM Corp, Armonk, NY, USA). The significance level applied to all analyses (and any adjustments for *post hoc* analyses) will be set at 0.05.

Analysis of the practitioner adherence checklist data will proceed using frequency counts to identify those areas addressed most frequently. This data will be interpreted with reference to the qualitative appraisal of feasibility and acceptability.

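### The Discussion promises a yes/no verdict on effectiveness that the protocol elsewhere disclaims and that a null result from this pilot could not support

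*Protocol article*

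**What the plan says.** The Discussion closes with a two-way verdict: "At the end of this study, we will have determined whether the intervention is effective or not".

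Other sections set a lower ambition:

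- Aims: "The primary aim of the study is to determine whether a family-relational-psychosexual intervention is feasible and acceptable for couples affected by prostate cancer". Subsidiary to this, the study is to "estimate the efficacy of the intervention to increase sexual and relationship functioning".
- Sample size calculation: the observed standardised difference "will be used to calculate the sample size required for a definitive trial to test the efficacy of this intervention". The same section calls the assumed effect size crude.
- Data collection: "As this is a feasibility study, it is not formally testing hypotheses". The outcome measures are to show an indicative effect.
- Statistical analysis: "Although hypothesis testing should proceed cautiously in a feasibility/acceptability study", followed by a list of expected directions of effect.

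Two places nevertheless rely on significance. The Statistical analysis section plans ANOVA and fixes a level: "The significance level applied to all analyses" is 0.05. The section on Phase 1 ties a commitment to participants to a test result: "The control group will be offered the intervention if the analysis indicates a significant benefit in quality of life".

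**The concern.** A reader of the Discussion expects a conclusion of effective or not effective. A reader of the Aims, Data collection and Sample size sections expects an estimate that feeds a later trial. Both cannot be right: if this study settled effectiveness, the definitive trial it is meant to size would have no efficacy question left.

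What is at stake is how the results may be read. A non-significant difference could be reported as showing that the intervention does not work, although the data would be compatible with the benefit the protocol itself names. A significant one could be reported as proof, although participants know their allocation, the outcomes are self-reported and there is one site. The waiting-list commitment under Phase 1 uses the same logic, since it depends on significance in a study said not to test hypotheses formally.

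**Working it through.** **Inputs.** From the Sample size calculation: 68 couples completing, f = 0.20, 90% power, alpha 0.05, two groups, two measurement points, SD 24, mean difference 9.6 units. From the Randomisation section: 1:1 allocation, hence 34 per arm. The correlation ρ between repeated measurements is not stated. I assume 0.5 to reproduce the sample size and vary it afterwards. Tests are taken as two-sided.

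**1. The plan's own figure.** For the within-between interaction, λ = f²·N·m/(1 − ρ) = 0.04 × 68 × 2 / 0.5 = 10.88, with 1 and 66 degrees of freedom. Power is 0.9015 (0.893 at N = 66), so 68 reproduces.

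**2. What that power refers to.** In a 2 × 2 interaction, f = 0.20 is a difference in change of 4·f·SD = 4 × 0.20 × 24 = 19.2 units. As a check, the SD of change at ρ = 0.5 is 24 × √(2 × 0.5) = 24. The standardised difference is therefore 19.2/24 = 0.8, and a t test with 34 per arm gives the same 0.9015. The stated 9.6 units is 2·f·SD = 2 × 0.20 × 24, half of that. The 90% does not apply to it.

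**3. Power for 9.6 units, unadjusted.** d = 9.6/24 = 0.4. The exact noncentral t with 34 per arm gives 36.9%.

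**4. Power for 9.6 units, favourable analysis.** This is ANCOVA on the mean of both follow-ups, with equal correlation ρ between all time points. Residual SD = 24 × √[(1 + ρ)/2 − ρ²].

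| ρ (assumed) | Residual SD | Power | 95% CI half-width |
|---|---|---|---|
| 0.5 | 16.97 | 63% | 8.2 |
| 0.6 | 15.92 | 69% | 7.7 |
| 0.7 | 14.40 | 77% | 7.0 |
| 0.8 | 12.24 | 89% | 5.9 |

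The article does not name this analysis.

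**5. What a null result could exclude.** Unadjusted half-width = t(0.975; 66) × 24 × √(2/34) = 1.997 × 5.82 = 11.6 units. Since 9.6 − 11.6 = −2.0, the interval would exclude a 9.6-unit benefit only if the point estimate favoured the control arm by more than 2 units. With ANCOVA at ρ = 0.5, the estimate would have to fall below 9.6 − 8.2 = 1.4 units, while any estimate up to 8.2 would be non-significant. Most of the non-significant positive range therefore leaves the target benefit open.

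**The case against.** The strongest reply is that the operative sections already say the right thing. The Aims, Sample size, Data collection and Statistical analysis sections all speak of estimation or caution, and the disputed clause is a closing remark that no analysis or decision rule refers to. That stands, and it limits the point to wording and consistency. It does not make the sentence true.

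A reader might infer more than the document supports:

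- *That the protocol forswears all testing.* It says it does not test formally and that testing should be cautious. Exploratory tests at 0.05 can be read alongside that.
- *That a p-value will end or adopt the intervention.* No such rule is written. The observed difference is used to size the next trial whether or not it is significant. Only the offer to waiting-list controls depends on significance.
- *That quality of life is not measured.* The Outcome measures section describes the primary measure as part of a wider health-related quality-of-life instrument. The term under Phase 1 is loose, but it has a link to EPIC.
- *That the false-positive risk for the verdict is about 19%.* 1 − 0.95⁴ = 18.5% counts HADS as two tests, assumes independence and lets any secondary result stand as a verdict. With three measures it is 14.3%, and EPIC is the single named primary outcome.
- *That the design can detect nothing.* A correctly specified test has about 90% power for some 19 units.

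The planned interaction test uses only the two post-treatment points and would miss a benefit that stays exactly constant between them. That is a separate matter. The same section also plans a comparison pre- and post-test, and nothing here depends on the interaction test.

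Lack of blinding follows from the type of intervention and would affect a definitive trial as well. It still limits what a positive result here may be called.

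**Conclusion.** The point holds as a contradiction and as an unsupported claim. The Discussion sentence cannot stand beside the Aims, Data collection and Sample size sections. A conclusion of ineffectiveness is out of reach for the effect the protocol names: power for 9.6 units is about 37% unadjusted and 63% to 89% under a favourable ANCOVA, and the unadjusted interval is wider than the target. A positive finding could be indicative, and a large one could be detected, but the setting and the nature of the outcomes argue against calling it a determination.

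The 37% rests on the protocol's SD of 24, 34 completers per arm and a two-sided 0.05 test. The ANCOVA range rests on an assumed correlation of 0.5 to 0.8 that is equal across time points. The contradiction itself needs no assumption.

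**What to change.** Replace the Discussion sentence. The new text should say that the study will estimate the effect on EPIC and the secondary outcomes with 95% confidence intervals, to inform a definitive trial, and that no conclusion of effectiveness or ineffectiveness will be drawn.

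Reconcile Phase 1 (the waiting-list commitment), Data collection and Statistical analysis on whether any decision depends on a significance test and, if so, on which outcome from the Outcome measures section. Which way the waiting-list commitment is settled is for the investigators.

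Criteria for proceeding to a definitive trial need not be added here, as an article may leave them to the full protocol.

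The cost is text only. Data, procedures and sample size are unchanged, and the study claims less.

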## Trial status

Open - currently recruiting participants.

## Abbreviations

ANOVA: repeated measures analysis of variance; EPIC: Expanded Prostate Cancer Index Composite; GP: general practitioner; GS: Gleason score; HADS: Hospital Anxiety and Depression score; MRC: Medical Research Council (United Kingdom); NHS: National Health Service (United Kingdom); PSA: prostate-specific antigen; RCT: randomised controlled trial; SCORE 15: systemic core outcome measure; TNM: tumour, node and metastases; UK: United Kingdom.
